## Abstract

**Introduction:**

Pregnant people have a higher risk of severe COVID-19 disease. They have been disproportionately impacted by COVID-19 infection control policies, which exacerbated conditions resulting in intimate partner violence, healthcare access, and mental health distress. This project examines the impact of accumulated individual health decisions and describes how perinatal care and health outcomes changed during the COVID-19 pandemic.

**Objectives:**

**Methods and analysis:**

This is a Canadian convergent parallel mixed-methods study. The quantitative strand uses a retrospective cohort design to assess birth group differences in rates of Tdap and COVID-19 vaccination, gestational diabetes screening, length of post-partum hospital stay, and onset of depression, anxiety, and adjustment disorder, using administrative data from ICES, formerly the Institute for Clinical Evaluative Sciences (Ontario) and PopulationData BC (PopData) (British Columbia). Differences by socioeconomic and ethnocultural status will also be examined. The qualitative strand employs qualitative description to interview people who gave birth between May 2020- December 2021 about their COVID-19 risk perception and health decision-making process. Data integration will occur during design and interpretation.

**Ethics and dissemination:**

This study received ethical approval from McMaster University and the University of British Columbia. Findings will be disseminated via manuscripts, presentations, and patient-facing infographics.

**Trial registration:**

**Registration:** Clinicaltrials.gov registration number: NCT05663762.

## Introduction

Pregnant people experience higher rates of COVID-19 hospitalization, intubation, and death compared to similar age and sex-matched peers who are not pregnant [1–3]. As in the general population, pregnant people who are racialized, low-income, or who live in high-density neighbourhoods have elevated COVID-19 infection rates [3, 4].

While there is little evidence specific to pregnant people, evidence about health care access and well-being in women, trans, and gender non-binary people helps us understand the circumstances faced in pandemic pregnancies. Most pregnant people identify as women, and women have been disproportionately impacted by the COVID-19 pandemic [5, 6]. Overall well-being of pregnant people has also been jeopardized by COVID-19 social isolation policies resulting in increased intimate partner violence [7–9] and mental health distress [10, 11]. During the pandemic, women experienced unemployment and income loss partly attributed to precarious employment and increased childcare responsibilities [12, 13]. Women were also overrepresented in designated essential service jobs with high levels of COVID-19 exposure (e.g., nursing and patient service occupations) [14]. Trans and non-binary people faced disproportionate pandemic-related challenges to mental health, violence, income loss, and access to healthcare compared to people of other genders [15, 16].

This project examines pregnant people’s health decisions within workplace, home, and community environments, describing their accumulated impact on key pregnancy outcomes and care indicators related to three themes: 1) vaccination, 2) perinatal care, 3) social supports and mental health. The decisions made during pregnancy have longitudinal impacts on the life of the pregnant person, future child, and family [17]. Given the likely unique and elevated health, social, and economic challenges faced by pregnant people during the pandemic, and the importance of health decisions during pregnancy, it is necessary to understand how pandemic circumstances have shaped decisions about accessing pregnancy-related healthcare. Understanding how and why pregnant people make health decisions allows for targeted clinical and social support as the pandemic endures and will inform future policy planning.

### Theme 1: Vaccination

Although pregnant people were not deliberately included in pre-market clinical trials, based on international immunization registry data [18], in May 2021 the Canadian National Advisory Committee on Immunization (NACI) recommended COVID-19 vaccination for pregnant people, with a preference for mRNA vaccines. Accordingly, pregnant populations were prioritized for access in late April (Ontario) and early May (British Columbia) 2021 [19, 20]. COVID-19 mRNA vaccines have shown a good safety profile during pregnancy [21], and protect against severe disease in the pregnant person as well as negative neonatal outcomes [22] including stillbirth [23] and infant hospitalization for COVID-19 [24].

Since 2018, Canadian guidelines have recommended that all pregnant people be offered pertussis vaccination (available via combination tetanus toxoid, diphtheria, and acellular pertussis, or Tdap, vaccine) [25, 26]. Uptake of routine (Tdap, influenza) vaccination during pregnancy in Canada has lagged behind that seen in comparator countries, but increased during the COVID-19 pandemic [27]. However, this overall increase obscures growing disparities (e.g., by ethnicity, income) and access barriers that may have been exacerbated by the pandemic [27]. Further, there have been indications of greater vaccination delay or refusal during pregnancy than in the general population, largely due to safety concerns [28, 29]. Factors commonly associated with low uptake of vaccination during pregnancy include socioeconomic status, demographic and geographic characteristics, access to prenatal care, and health literacy [30–32]. While a recommendation from a trusted prenatal care provider is typically understood to be one of the strongest influences for vaccine uptake [32–36], limited in-person appointments may have weakened that influence during the pandemic. We do not yet know how vaccine uptake has changed, including how decreased access to in-person prenatal care may have influenced decisions regarding vaccines recommended in pregnancy.

### Theme 2: Perinatal care

Perinatal care includes medical care delivered during the prenatal, intrapartum and postpartum periods. Routine prenatal care consists of a series of regular interactions with a health care provider–typically a family physician, midwife, and/or obstetrician (OB)–for education, screening, and treatment interventions [37]. Inadequate prenatal care has been associated with a number of negative health outcomes, including stillbirth, pre-term birth, low birth weight, NICU admission, and postpartum depression and anxiety [38]. The COVID-19 pandemic instigated many changes to the delivery of routine prenatal care related to the incorporation of telephone or virtual visits [39–41], and changes to prenatal care schedules to adapt to re-allocation of healthcare resources, personal protective equipment limitations, and lack of continuity of care from the same prenatal care provider [42]. Perinatal care also changed in relation to policies that reduced support persons and visitors, and exacerbated other access issues related to childcare, precarious work, and transportation [43–45]. There are little data about the outcomes associated with these changes to prenatal care delivery, with some studies finding no difference in maternal and infant health outcomes [46, 47] and others in a global meta-analysis demonstrating shorter in-hospital stays after delivery, less prenatal care attendance, lower participation in screening for infection, anemia and fetal anomaly [47]. We do not know how these changes to the delivery of prenatal care influenced features such as uptake of gestational diabetes screening, or the duration of postpartum hospitalization in Canada. Further, it is unknown whether any changes in healthcare access that may have occurred reflected patient choice or influenced patient experience.

### Theme 3: Mental health and social support

Untreated antenatal depression and anxiety are associated with pre-term birth, low birth weight, and increased risk of infant hospitalization and death within the first year of life [48, 49]. A systematic review and meta-analysis of global data indicate high rates of prenatal depression (30.5%) and anxiety (25.6%) during the COVID-19 pandemic [50]. Pregnant people in Canada may experience even higher rates of depression and anxiety [51], perhaps in response to concerns about threats of COVID-19 to themselves or their fetus, insufficient prenatal care, strained relationships, and social isolation [52]. Mental health concerns may be greater for those who experienced extra stress or safety fears due to income disruptions, difficulties balancing childcare and work responsibilities, are single parents, or had difficulty obtaining childcare [11, 53, 54]. The stress and anxiety experienced during the pandemic may have contributed to lower birth weights, younger gestational age at birth, and other birth-related issues [42, 52]. So far, there are little data about how perinatal mental health diagnosis rates have changed throughout the pandemic. We do not know whether any observed changes in mental healthcare use reflect barriers to accessing care. We do not know how pregnant people experienced their feelings of depression and anxiety, and how they chose to cope with these experiences.

## Objectives, questions and hypotheses

This research study has two objectives:

Evaluate potential associations between exposure(s) and outcome(s) for births occurring in 2019 (Jan 1 2019 –Mar 31 2019 births), 2021 (Jan 1 2021 –Mar 31 2021 births), and 2022 (Jan 1 2022- Mar 31 2022 births) birth groups in Ontario and BC related to vaccination, perinatal care, and mental health, overall, by race/ethnicity and by income. *(Quantitative strand)*Understand how people who gave birth in Ontario or BC in 2020 or 2021 perceived COVID-19 risk and how pandemic circumstances influenced their decision-making about key elements of pregnancy, including vaccination, perinatal care, social support and mental health. *(Qualitative strand)*

Research questions and hypotheses have been operationalized according to our three themes:

### Theme 1: Vaccination

Quantitative Research Question (RQ): Were rates of vaccination different between 2019, 2021, and 2022 birth groups? What factors are associated with vaccination rates? **Outcomes:** Tdap (ON) and COVID-19 (ON and BC) vaccination rates
○ Hypothesis 1.1: 2019 group will have a higher rate of Tdap vaccination than the 2021 and 2022 groups.○ Hypothesis 1.2: COVID-19 vaccination rates in the 2022 group will be lower than those of the comparable overall female population in each province.○ Hypothesis 1.3: In the 2022 group, pregnant persons who receive Tdap vaccination will be more likely to receive COVID-19 vaccination than those who do not receive Tdap vaccination. (Ontario only due to data availability)Qualitative RQ: How have pregnant people’s choices about Tdap and COVID-19 vaccination been influenced by perceptions of COVID-19 risk, COVID-19 policies and personal socioeconomic circumstances during the pandemic (“pandemic circumstances”)?
○ How do personal identities and circumstances (e.g., race, education, age, income, presence of other children in the home) affect these decision-making processes?

### Theme 2: Perinatal care

Quantitative RQ: Were rates of in-person perinatal care different between 2019, 2021, and 2022 pandemic groups? What factors are associated with in-person perinatal care? **Outcomes:** Gestational diabetes screening, maternal post-partum length-of-stay (BC and ON)
○ Hypothesis 2.1: 2021 group will have lower rates of gestational diabetes screening than the 2019 or 2022 groups.○ Hypothesis 2.2: 2019 group will have longer length of hospital stay after delivery than 2021 or 2022 groups.Qualitative RQ: How have pregnant people’s decisions about seeking prenatal care and planning for birth been influenced by perceptions of COVID-19 risk?
○ How do personal identities and circumstances (e.g., race, education, partnered status, presence of other children in the home) affect risk perception and decision-making processes?

### Theme 3: Mental health and social support

Quantitative RQ: Were the rates of clinical diagnosis for new depression, anxiety, and adjustment disorders during pregnancy and up to six months postpartum different between 2019, 2021, and 2022 birth groups? What factors are associated with this clinical diagnosis? **Outcomes:** New onset of depression, anxiety and/or adjustment disorder diagnosis during pregnancy and six months postpartum (ON and BC) validated by Frey and colleagues [55].
○ Quantitative hypothesis 3.1: 2019 group will have lower rates of new clinical diagnosis for depression, anxiety, or adjustment disorder than 2021 and 2022 groups.Qualitative RQ: How do pregnant people describe the relationship between their perceptions of COVID-19 risk, experiences of mental health, and decisions about seeking social support during pregnancy?Qualitative RQ: How do pregnant people describe their decisions to balance COVID-19 protocols (e.g., masking, limiting social contact) with their physical, mental, and social needs? How do personal identities and circumstances (e.g. race, education, household composition) affect these decision-making processes?

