#### Study population

Our cohort for the quantitative portion will be defined by three groups according to the date they gave birth: January 1 to March 31, 2019; January 1 to March 31, 2021; and January 1 to March 31, 2022 (Fig 1). These groups represent gestation before the pandemic, gestation during the pandemic but before widespread vaccine availability, and gestation after widespread vaccine availability. These timeframes reflect an assumption that in the experience of pregnant people in Ontario and BC, the pandemic “started” with the enactment of public health measures in mid-March 2020. While the three-month birthing window excludes large portions of the year, this approach is necessary to construct groups within each time period that have no overlap in gestational periods. Overlapping gestational periods would result in cohort members being exposed to multiple time periods, leading to bias in our results. These groups are standardized by birth month to reflect evidence of seasonality in birth rates and health outcomes [57, 58].

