#### Outcomes

We will use COVaxON in ICES and COVID-19 Immunization Data in PopData to define our COVID-19 vaccination outcome. Tdap vaccination status will be derived from the Ontario Laboratory Information System (OLIS); Tdap records are not available in PopData. OLIS and the MSP dataset in BC will define gestational diabetes screening outcomes. The Discharge Abstract Data (DAD) will provide data for our postpartum length-of-stay outcome. New onset of depression, anxiety or adjustment disorder will be ascertained using Ontario Health Insurance Plan (OHIP) diagnostic codes from physician billing claims, the DAD, and the Ontario Mental Health Reporting System (OMHRS) in Ontario; the BCPDR and physician billing claims report cases of depression, mood and anxiety. The timeframes of interest for our outcomes are illustrated in Fig 2.

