## Strengths and limitations

This study has several strengths. The large administrative datasets offer significant statistical power to investigate changes in health care use, stratified by markers of socioeconomic and ethnocultural status. The cross-provincial nature of our analysis allows the observation of consistency or change based on different healthcare policies, vaccine availability, medical care provision, and COVID-19 burden. The integration with qualitative data offers the potential for explaining observed differences. Our study team incorporates multiple individuals with lived experience of a pandemic pregnancy, and frontline clinicians who cared for pregnant people in both provinces during the pandemic.

This study has some limitations. Relying on administrative data hinders the ability to gather some data points of interest. For example, neither ICES or PopData have patient-level demographic data about race or socioeconomic status. Instead, we will rely on area-level data abstracted from the 2016 Canadian Census, operationalized through the CIMD. The administrative datasets exclude some births, such as those which took place outside of a hospital setting. Qualitative data will be gathered from people who gave birth between May 1, 2020 to Dec 1, 2021, which may introduce some challenges with recall and social desirability bias. However, our co-investigators with lived experience assure us that due to the unique and challenging nature of these decisions, they are able to recall their decision-making very clearly.

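### The mental-health outcome mixes vaccine periods for the 2021 v 2022 comparison and is described differently in Ontario and BC; the H3.1 contrasts with 2019 are not affected

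*Protocol article*

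**What the plan says.** **Outcome and question.** Theme 3 under Objectives defines the outcome as "New onset of depression, anxiety and/or adjustment disorder diagnosis during pregnancy and six months postpartum (ON and BC". The research question asks whether rates were "different between 2019, 2021, and 2022 birth groups? What factors are associated with this clinical diagnosis". Hypothesis 3.1 is narrower: "2019 group will have lower rates of new clinical diagnosis for depression, anxiety, or adjustment disorder than 2021 and 2022 groups". The Inferential section lists new onset among the binary outcomes for logistic regression. The notes on outcome timeframes list a gestation window (A, conception to birth) and a postpartum window (B, birth to six months). The article does not say that the two are analysed separately.

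**Groups.** Study population sets the birth windows as "January 1 to March 31, 2019; January 1 to March 31, 2021; and January 1 to March 31, 2022" and says that they stand for "gestation before the pandemic, gestation during the pandemic but before widespread vaccine availability, and gestation after widespread vaccine availability". It justifies the short windows thus: "Overlapping gestational periods would result in cohort members being exposed to multiple time periods, leading to bias in our results".

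**Sources.** For Ontario, the Outcomes section names physician billing codes, hospital discharge abstracts (DAD) and the mental health reporting system (OMHRS), for depression, anxiety or adjustment disorder. For BC it says that "the BCPDR and physician billing claims report cases of depression, mood and anxiety". Strengths and limitations adds: "The cross-provincial nature of our analysis allows the observation of consistency or change".

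**The concern.** There are two separate problems.

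**Time.** The plan gives up nine months of births per year so that gestations do not span more than one period. It then measures this outcome for a further six months after birth. For births in January to March 2021, those months run to between 1 July and 30 September 2021. The vaccine had by then been opened to pregnant people, and the 2022 group was already pregnant. A 2021 v 2022 difference in the combined outcome is therefore not a clean pre- v post-vaccine difference, and the shared calendar time would tend to shrink it. The limitations do not mention this.

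**Province.** Theme 3 promises one outcome for both provinces. The Outcomes section names adjustment disorder for Ontario only, adds mood for BC, and names neither DAD nor a mental-health reporting source for BC's mental-health outcome. If the two rates are set side by side, a gap in level could come from how cases are found and not from care or health.

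**Working it through.** **1. The plan's own figure.** The quantitative Sample size section gives about 140,000 births a year in Ontario and 42,000 in BC. 140,000 × 1/4 × 3 = 105,000 and 42,000 × 1/4 × 3 = 31,500, as stated. Together that is 136,500.

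**2. Postpartum time after the vaccine cut-off, 2021 group.** Inputs:
- Births are spread evenly over 1 January to 31 March 2021, days 1 to 90 of the year, mean 45.5 (assumed).
- Six months are 182 days, and conception is 266 days before birth (40-week pregnancy, assumed). The whole window is 266 + 182 = 448 days.
- The article gives no date for wide availability. As a proxy I take the opening of access to pregnant people, which the Introduction (Theme 1) puts in late April (Ontario) and early May (BC) 2021. Cut-offs of 20 April, 1 May and 10 May are days 110, 121 and 130.

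Postpartum days after cut-off day d for a birth on day b number b + 182 − d. Dividing by 182 gives the postpartum share, and by 448 the share of the whole window.

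| Cut-off | Postpartum, mean | First to last birth | Whole window, mean |
|---|---|---|---|
| 20 April | 117.5/182 = 65% | 73/182 = 40% to 162/182 = 89% | 117.5/448 = 26% |
| 1 May | 106.5/182 = 59% | 62/182 = 34% to 151/182 = 83% | 106.5/448 = 24% |
| 10 May | 97.5/182 = 54% | 53/182 = 29% to 142/182 = 78% | 97.5/448 = 22% |

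Every 2021 member has postpartum time on both sides of each cut-off.

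**3. Overlap with the 2022 group's gestation.** Conceptions in that group run from about 10 April 2021 (266 days before 1 January 2022) to 8 July 2021. The share of the 2021 group's postpartum time on or after 10 April (day 100) is (45.5 + 182 − 100)/182 = 127.5/182 = 70%.

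**4. How far 2021 and 2022 are separated.** Share of time after the cut-off:
- Window A: 2021 has 0% and 2022 has 98-100%, a gap of 98 to 100 points.
- Window B: 2021 has 54-65% and 2022 has 100%, a gap of 35 to 46 points.
- Combined: 2021 has 22-26% and 2022 has 99-100%, a gap of about 74 points (100 − 26) to 77 points (99 − 22).

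**5. The contrasts in H3.1.** With the pandemic start at mid-March 2020, as Study population assumes, the 2019 group has 0% pandemic time in both windows (about April 2018 to September 2019). The 2021 and 2022 groups have 100% in both. The windows match in season and length.

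**6. Province difference (illustration).** No outcome rate or capture rate is in the text, so both are assumed: a true rate of 15% in both provinces, with BC missing 5%, 10% or 20% of cases.
- Observed BC rate: 15% × 0.95 = 14.25%; × 0.90 = 13.5%; × 0.80 = 12.0%.
- Apparent BC v Ontario odds ratio, for example (0.135/0.865)/(0.15/0.85) = 0.88; the other two are 0.94 and 0.77.
- With 105,000 v 31,500 births and a two-sided 5% test, the chance of a significant but spurious difference is 91% when 5% are missed and above 99% when 10% or more are. For true rates of 10% to 20%, the 5% case ranges from 74% to 98%.

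The direction is not known, because the added mood category could raise the BC count instead.

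**7. Within BC.** If a constant fraction k is captured, the risk ratio between birth groups is (k × p2)/(k × p1) = p2/p1, unchanged. The planned logistic model gives odds ratios, which move only slightly. For 18% v 15% the true odds ratio is (0.18/0.82)/(0.15/0.85) = 1.244. With 10% missed it is (0.162/0.838)/(0.135/0.865) = 1.239.

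**The case against.** A reader might infer that no birth-group comparison of this outcome is like with like, or that H3.1 fails. The documents do not support that. H3.1 sets 2019 against 2021 and against 2022, and step 5 shows both contrasts to be cleanly pre-pandemic v pandemic. Nor does the plan break its own rule: the rationale and all three labels in Study population concern gestation. The postpartum overlap limits interpretation of 2021 v 2022, which only the broader research question raises.

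The article also already defines windows A and B, and the choice to model them separately could be left to an analysis plan that is not shown. That stands in part. But Theme 3 and the Inferential section both describe one new-onset outcome, and nothing in the article says which window carries the pre-/post-vaccine reading.

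On the provinces, no pooled model or cross-province hypothesis on these rates is stated, and consistency or change can be read as comparing patterns within each province. That stands too: a stronger claim, that differences in change are also uninterpretable, fails if capture is constant over time (step 7). The BC sentence may be condensed, and S1 Table and Fig 2, which are not shown, may name more sources. BC's lack of adjustment disorder or DAD for this outcome is thus read from silence. What remains is that two sections of the same article describe the BC outcome differently.

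**Conclusion.** The point holds in a limited form. About 54-65% of the 2021 group's postpartum time, and 22-26% of its whole outcome window, lies after vaccine access opened to pregnant people. This blurs the 2021 v 2022 comparison, mildly in the combined outcome and heavily in the postpartum part. H3.1 is unaffected. These shares rest on evenly spread births, a 40-week pregnancy and a cut-off between 20 April and 10 May 2021.

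The BC and Ontario descriptions do not match, so a difference in level between provinces cannot be interpreted as it stands. The size of that effect is unknown, and the odds ratios of 0.77 to 0.94 are illustrations on assumed figures. Within-province ratios are safe as long as the difference in capture does not change over time.

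**What to change.** 1. Keep the combined outcome for H3.1, so that the stated question, pregnancy plus six months, is answered in full.
2. Also report and model windows A and B separately. Base any pre-/post-vaccine reading of 2021 v 2022 on A, and describe B as mixed-period for the 2021 group.
3. Reconcile the Theme 3 outcome with the BC wording in Outcomes: say which diagnosis groups and sources apply in BC.
4. Make any cross-province statement on a common diagnosis set from sources held in both provinces: physician billing, plus DAD where available. DAD is already named for length of stay, an outcome listed for both provinces. Keep the fuller definitions, including OMHRS and the BC perinatal registry, for within-province analyses. Otherwise state that the results are province-specific.

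The cost is some wording, code lists and a few more models on sources already named. Each component will have fewer events than the combined outcome, which matters little with about 136,500 births. Restricting H3.1 to gestation would be a worse trade, since it drops the postpartum half of the question without need.
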